## Abstract

**Background:** Depressive and anxiety disorders are highly prevalent, but only a small percentage (approximately 50%) of patients receive appropriate treatment. Relevant barriers include communication and coordination gaps between different providers that result from the lack of integration between different care-giving systems. Aftercare following inpatient treatment represents one of these gaps because systematic follow-up care does not exist. Case management-based aftercare coordination by phone might be a promising approach to overcoming this gap and improving long-term treatment outcomes. Case management is a patient-centered and situation-based approach comprising systematic tracking and support of patients by a case manager. The aim of this study is to evaluate the effectiveness of aftercare coordination by phone for patients with depressive and anxiety disorders.

**Methods/design:** The effectiveness of aftercare coordination will be investigated in a prospective randomized controlled trial in four psychotherapeutic inpatient routine care units (St. Franziska-Stift Bad Kreuznach, MediClin Seepark Klinik Bad Bodenteich, Segeberger Kliniken Gruppe Bad Segeberg and Luisenklinik Bad Dürkheim). The patients receiving aftercare coordination (intervention group; IG) will be compared with those who receive treatment as usual (TAU control group; CG). Eligible patients will be required to have a diagnosis of an anxiety and/or depressive disorder and a recommendation for follow-up outpatient psychotherapy.

The aftercare coordination consists of six phone contacts at intervals of two weeks that are performed by therapists in the inpatient units. The patients will complete questionnaires at discharge ( $t_1$ ), 3 months after discharge (i.e., at the end of the intervention ( $t_2$ )) and 9 months after discharge ( $t_3$ ). The primary outcome will be change in symptom severity from  $t_1$  to  $t_3$ , the secondary outcomes will be health-related quality of life and the proportion of patients who manage to begin outpatient psychotherapy by  $t_3$ .

**Discussion:** This study will determine whether case management-based aftercare coordination by phone is an adequate approach for overcoming treatment barriers in the clinical pathways of patients with depressive and anxiety disorders. If proven effective, an accessible supplementary treatment approach that will help to maintain and even improve long-term treatment outcomes will be made available for patients following inpatient treatment.

**Trial registration:** ClinicalTrials.gov: (NCT02044913).

**Keywords:** Randomized controlled trial, Aftercare, Case management, Phone-based, Depression, Anxiety, Evaluation, Effectiveness

\* Correspondence: [contact]

†Equal contributors

Department of Medical Psychology, University Medical Center  
Hamburg-Eppendorf, [name], Germany  
Full list of author information is available at the end of the article

## Background

Depressive and anxiety disorders are among the most prevalent mental disorders and cause significant personal, social and economic burdens. Despite the high 12-month prevalence rates of 15.3% for anxiety and 7.7% for depression in Germany [1] only approximately half of these patients receive appropriate treatment [2]. This finding is indicative of undertreatment and the need for the optimization in the care of patients with anxiety and depression. Significant barriers in the patients' pathways include communication and coordination problems between different services or providers [3-6]. The aftercare following inpatient treatment represents one of these gaps. After inpatient treatment, follow-up outpatient psychotherapy is clinically indicated for the majority of patients with anxiety and depressive disorders [7]. Here, the aims are to consolidate the treatment outcomes and to minimize the so-called rebound-effect, i.e., the long-term reduction in positive treatment effects following inpatient treatment. Although there is evidence supporting the effectiveness of inpatient treatment, treatment effects often decrease after treatment. A portion of patients who exhibit improvements at termination relapse and continue to seek help from a variety of mental health providers [8]. Depressive disorders are particularly highly recurrent, and the risk of a further episode increases with each additional episode; thus, the prevention of relapse is extremely desirable [9]. It can be assumed that the therapeutic alliance represents a protective factor against rebound effect; numerous studies have found that the therapeutic alliance is relevant to the outcome of psychotherapy [10] and the prevention of relapse [11]. However, the high risk of relapse indicates that follow-up support, e.g., outpatient psychotherapy, is necessary for patients to maintain long-term treatment outcomes after returning to everyday life. In addition to outpatient psychotherapy and primary and specialist care, patients can also profit from low-intensity offerings such as self-help groups and counseling. Thus, several aftercare treatment options exist, but many patients do not access follow-up treatment. Treatment barriers that result from a lack of integration of the different steps in care can occur on the systemic level (e.g., long waiting times for outpatient psychotherapy) and on the individual level (e.g., insufficient patient awareness of available treatments) [6].

Case management-based aftercare coordination by phone might be a promising approach to overcoming the gap between inpatient treatment and aftercare. Case management is a patient-centered and situation-based approach comprised of systematic tracking and support of patients by a case manager. The primary goal is to coordinate and integrate services across treatment settings by providing self-managing support and follow-up for patients [3].

Previous international research on the effectiveness of case management has consistently reported positive effects on treatment outcomes, e.g., symptoms, quality of life and patient satisfaction [12-14]. However, in Germany, case management programs for anxiety and depression have not yet been implemented. Because the German health-care system differs significantly from the systems of other countries, the transferability of results from international studies still requires to be verified [14]. Furthermore, the various case management-based approaches differ concerning their content and the health care setting in which they are implemented. The first effectiveness study of a case management model for patients with depression in the German health care system reported that phone-based case management in primary health care results in better treatment outcomes compared to regular care in terms of symptom reduction, medication adherence and patient satisfaction [15]. Here, the intervention focused on monitoring depression symptoms, adherence to medication and encouraging the patients to follow self-managing activities and engage in pleasant or social activities. In this study, the focus of the intervention will be on the coordination of an adequate aftercare for patients with anxiety and depressive disorders.

## Objectives

This study aims first to evaluate the effectiveness of aftercare coordination by phone following inpatient treatment for patients with anxiety and depression. The primary outcome will be change in symptom severity from  $t_1$  to  $t_3$ , and the secondary outcomes will be health-related quality of life, self-efficacy and the proportion of patients who managed to begin outpatient psychotherapy at follow-up (6 months after the intervention). Whether the patients who receive the aftercare coordination (i.e., the intervention group; IG) exhibit better treatment outcomes at the terminations of the intervention and follow-up compared to the patients who receive treatment as usual (TAU, i.e., the control group; CG) will be examined. Second, whether patient characteristics can predict the outcomes of aftercare coordination will be examined. Third, whether the therapeutic alliance during inpatient treatment has moderating effects on the primary and secondary outcomes will be examined. Fourth, different anxiety-specific measures will be assessed to determine the changes in the symptom severities in patients with different anxiety disorders. Fifth, process evaluation will be conducted to identify the main contents of the aftercare coordination and to determine whether the patients benefit during the course of the intervention from the perspective of the therapists. Finally, the patients' satisfaction with the case management procedures and acceptance of the intervention will also be assessed.

### Ethical approval

The study has been approved by the responsible local Ethics Committee of the Chamber of Physicians in Hamburg (Ref. Nr. PV4004) and will be conducted according to the principles of the Declaration of Helsinki (2013 version).

### Methods/design

#### Study design

The study will be performed as prospective multicenter randomized controlled trial (Figure 1). The patients who receive aftercare coordination by phone (IG) will be compared to those who receive TAU without aftercare coordination by phone (CG). Measurements will be performed at three time points in each group. Baseline measures will be taken at discharge from the inpatient treatment (which will be the beginning of the intervention;  $t_1$ ), and two follow-up measures will be taken after 3 months at the end of the intervention ( $t_2$ ) and again 6 months after the end of the intervention (which will be 9 months after discharge from inpatient treatment;  $t_3$ ).

#### Trial inclusion and exclusion criteria

The included patients will be required to be at least 18 years old and have a diagnosis of anxiety (F40.x, F41.x, according to ICD-10) [16] and/or depressive disorder (F32.x, F33.x, F34.1). The diagnoses will be validated with the Mini-DIPS diagnostic interview [17], which is a short version of the DIPS diagnostic interview for mental disorders [18]. Comorbid mental disorders or somatic comorbidity will not be an exclusion criterion.

Patients who are already in a concurrent outpatient psychotherapeutic treatment at admission that will be continued after the inpatient treatment will be excluded from the study because aftercare coordination will not be necessary for those patients. Further exclusion criteria include acute risk of suicide, acute psychosis or psychotic symptoms, insufficient German language skills and an inpatient treatment duration of less than three days.

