### Recruitment and data collection

The patients who fulfill the study inclusion criteria will be recruited consecutively by their therapists at the beginning of their inpatient treatment in the four cooperating psychotherapeutic inpatient units (St. Franziska-Stift Bad Kreuznach, MediClin Seepark Klinik Bad Bodenteich, Segeberger Kliniken Gruppe Bad Segeberg and Luisenlinik Bad Dürreheim). Prior to participation, the patients will be informed with oral and written information regarding the study by their therapists. After written informed consent is obtained, the patients will be randomly assigned to the IG or the CG.

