#### Randomization

The patients will be randomized using a stratified block randomization with randomly varying block size to ensure concealment and equal group sizes, and the randomization will be stratified by the participating clinical units. The randomization will take place at the individual level at the University Medical Center Hamburg-Eppendorf one week before the beginning of the intervention. The allocation schedule was created with a computer program (Microsoft Excel, Windows) by a researcher at the University Medical Center Hamburg-Eppendorf. The therapists will be informed about the randomization outcome prior to the last psychotherapeutic session during inpatient treatment so that they can inform the patients about their group assignment before discharge.

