#### Secondary outcome measures

The secondary outcomes include health-related quality of life as measured with the EuroQol-5D [20] and the Short Form 8 Health Survey (SF8) [21]. The >EuroQol-5D is a generic instrument that measures health-related

quality of life in five dimensions; i.e., mobility, self-care, usual activities, pain/discomfort and anxiety/depression. Health-related quality of life will also be assessed with a visual analogue scale (range: 0 to 100; higher ratings indicate higher quality of life). The SF-8 is a short version of the SF-36 [22] allows for the calculation of scores for physical and mental health (range: 0 to 100; higher scores indicate better statuses). This instrument has good psychometric properties with an internal consistency between .70 and .88 [23].

As an additional secondary outcome, the proportion of patients who managed to organize outpatient psychotherapy at follow-up will be assessed with self-report items. Whether self-efficacy can be improved by the case management-based intervention that aims to empowering the patients to become active will also be investigated. The German General Self-Efficacy Scale (SWE) [24] will be used to assess self-efficacy. This scale comprises 10 four-point Likert-scale items that range from 1 ('totally disagree') to 4 ('totally agree'). The questionnaire includes items such as "If there are challenges, I can find a way to succeed" and "I can find a solution for every problem". The summed scores range between 10 and 40, and higher scores indicate greater general self-efficacy. The internal consistency of this instrument ranges from .80 to .90 [24].

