### Additional measures

To investigate whether patient characteristics can predict the outcomes of aftercare coordination, the following demographic and clinical characteristics will be collected via a self-report questionnaire: age, gender, marital status and partnership, children, level of education, employment status and occupational situation, and medical and psychosocial treatment prior to the inpatient treatment. To examine whether the therapeutic alliance is associated with the primary outcome, the therapeutic relationship will be measured with the Helping Alliance Questionnaire (HAQ-S) [25], which consists of 11 items that are rated on a six-point Likert scale ranging from -3 ('strongly disagree') to 3 ('strongly agree'). A total score is calculated, and higher total scores are indicative of better alliances. Research has demonstrated the good reliability and validity of this instrument [26].

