the intervention, it is not the primary or only criterion of success. Depending on the structural circumstances in the health care system, there might be situations in which it is not possible to initiate an adequate aftercare treatment, e.g., in cases of long waiting times for outpatient psychotherapy [37], within the three month of the intervention. However, there are several potential aftercare treatment possibilities other than outpatient psychotherapy and primary and specialist care, including low-threshold offers, e.g., self-help groups and consulting centers, from which the patients can benefit. Therefore, the likelihood of initiating adequate aftercare should be reasonable. However, the main aim of the intervention is to provide the patients with tools that enable them to continue organizing their aftercare themselves. Presumably, in addition to symptom severity, health-related quality of life and self-efficacy will also be improved by the case management-based intervention; therefore, these latter parameters will also be included as secondary outcome measures. Learning to manage aftercare treatment successfully themselves might be an experience that promotes feelings of satisfaction and self-efficacy in the patients. As an additional secondary outcome, the proportion of patients who managed to begin outpatient psychotherapy at follow-up will be assessed. It is expected to be higher in the IG than in the CG due to the supporting aftercare intervention. Presumably, the study will have high external validity because the participants will be consecutively recruited from routine care and routine clinical settings. If the intervention is found to be effective and accepted by the patients and professionals, an accessible supplementary treatment approach that can help to overcome barriers in the clinical pathways will be made available for patients following inpatient treatment. Treatment barriers due to the lack of integration of the different caregiving systems are common problems in the German health care system [5]. Therefore, aftercare coordination could also be adapted to the needs of and applied to patients with other mental disorders and chronic diseases.

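### Patients who already hold an outpatient psychotherapy place at randomisation stay eligible and dilute the secondary access outcome; record that status before allocation and stratify on it

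*Protocol*

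**What the plan says.** - **Eligibility.** Under Trial inclusion and exclusion criteria: "Patients who are already in a concurrent outpatient psychotherapeutic treatment at admission that will be continued after the inpatient treatment will be excluded", with the reason "because aftercare coordination will not be necessary for those patients". The Abstract adds that patients need "a recommendation for follow-up outpatient psychotherapy". A patient can have both that recommendation and a place.
- **Timing.** Under Recruitment and data collection, patients are "recruited consecutively by their therapists at the beginning of their inpatient treatment". Under Randomization, allocation happens "one week before the beginning of the intervention". Study design starts the intervention at discharge, which is also t1. Patients are to learn their group before discharge.
- **Outcome.** Under Secondary outcome measures: "the proportion of patients who managed to organize outpatient psychotherapy at follow-up will be assessed with self-report items". The Abstract, Objectives and Discussion instead count patients who begin outpatient psychotherapy. Neither wording limits when the place was arranged. The Discussion says of this proportion: "It is expected to be higher in the IG than in the CG due to the supporting aftercare intervention".
- **Baseline data.** Additional measures lists, among the self-reported characteristics, "medical and psychosocial treatment prior to the inpatient treatment". It names no item on a place arranged for after discharge. Randomisation is stratified by clinical unit only.

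**The concern.** The reason given for the exclusion applies in large part to a patient who has an agreed place that has not yet started, but the criterion does not reach that patient. A place found during the stay, between recruitment and randomisation, is not covered either.

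The access outcome is meant to show what the phone contacts add. Under the organise wording, a place-holder is a success before allocation, whatever the arm. Under the begin wording, a place-holder will probably succeed in both arms. Either way, both proportions rise and the difference between them shrinks. The Discussion calls starting outpatient treatment the decisive aim of the intervention, although not its primary or only criterion of success. What is at stake is therefore the power of the outcome closest to the mechanism. The primary result is not affected.

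**Working it through.** **The plan's own figure.** Power calculation uses f = 0.29, so d = 2 × 0.29 = 0.58. A two-sided t-test at 0.05 with 80% power needs a total of 95.3, rounded to 48 per arm (N = 96). With 50% dropout, 96 / 0.5 = 192. Both stated figures reproduce. They concern the BDI-II; the protocol states no rate, sample size or power for the access outcome.

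**Inputs for the access outcome.**
- From the protocol: 96 per arm randomised, 48 per arm after the expected dropout, alpha 0.05 (taken as two-sided).
- Assumed, because the protocol gives neither: the share q of place-holders, varied from 0 to 40%, and access rates of 60% (intervention) and 40% (control) among patients without a place.

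**Dilution.** If every place-holder counts as a success in both arms, each observed proportion is q + (1 − q)p. The difference is then (1 − q)(0.60 − 0.40).

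**Power, unadjusted.** Φ{[d√n − 1.96√(2p̄(1 − p̄))] / √[p₁(1 − p₁) + p₂(1 − p₂)]}, where d is now the difference in proportions. At q = 20% and n = 96:
- proportions 0.20 + 0.80 × 0.60 = 0.68 and 0.20 + 0.80 × 0.40 = 0.52, so d = 0.16 and p̄ = 0.60;
- (0.16 × 9.798 − 1.96 × 0.693) / 0.684 = 0.307, giving power 62%.

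**Power, all randomised patients, stratified by place status.** Place-holders who all succeed add neither effect nor variance, so the test has the information of the 96 × 0.80 = 76.8 patients per arm without a place. (0.20 × √76.8 − 1.96 × 0.707) / 0.693 = 0.529, giving power 70%.

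| q | Difference (points) | Unadjusted, 96 per arm | Stratified, 96 per arm | Unadjusted, 48 per arm |
|---|---|---|---|---|
| 0% | 20 | 80% | 80% | 50% |
| 10% | 18 | 71% | 75% | 42% |
| 20% | 16 | 62% | 70% | 36% |
| 30% | 14 | 53% | 64% | 30% |
| 40% | 12 | 44% | 58% | 25% |

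Other assumed rates show the same pattern. With 50% versus 30% and 96 per arm, unadjusted power is 81% at q = 0, 60% at 20% and 41% at 40%. With 70% versus 50% it is 81%, 66% and 49%.

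**If coordination also helps place-holders take up their place.** Assume 95% versus 85% of them start, with q = 20%. The proportions are 0.20 × 0.95 + 0.80 × 0.60 = 0.67 and 0.20 × 0.85 + 0.80 × 0.40 = 0.49, a difference of 18 points. With 96 per arm, power is 72% unadjusted, 77% stratified, and 70% if only patients without a place are analysed.

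**The case against.** Several points on the other side stand, and they limit what can be claimed.

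- **A reader might infer that every place-holder is a success before allocation.** That holds only under the organise wording. Under the begin wording the patient must still start, and the intervention's monitoring and encouragement could help with that. Dilution is then less than the full share.
- **A reader might infer bias between the arms.** The documents do not support this. Randomisation balances place-holders on average, and the all-randomised difference is a valid effect in the consecutively recruited routine-care population that the Discussion wants.
- **A reader might infer that the outcome should be analysed mainly in patients without a place.** That answers a different question, so it is a choice of estimand. In the take-up scenario above, it also has less power than no adjustment at all.
- **A reader might infer that place status is certainly never recorded.** The list under Additional measures need not be the whole questionnaire, and the self-report items are not reproduced. What can be said is that the protocol does not show it is recorded. A later analysis plan cannot recover a pre-allocation fact that was not collected.
- **The share may be small.** Background and Discussion describe long waiting times, and Background says that many patients do not access follow-up treatment.

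The objection does not remove the gap itself. The criterion as worded leaves place-holders in, neither outcome wording sets them apart, and the remedy is cheap.

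**Conclusion.** The point holds as a limited weakness in one secondary outcome. Patients with a place arranged before randomisation are eligible and raise the access proportion in both arms. The difference shrinks by up to the share q, by exactly that share if coordination makes no difference to them and by less if it does.

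The size is unknown, because the protocol gives neither q nor any access rate. Under the assumed 60% versus 40% with 96 per arm, stratifying on place status recovers about 4 power points at q = 10%, 8 at 20% and 11 at 30%. With the expected 50% dropout, power for this outcome is low in any case (50% at q = 0), which is a reason not to lose more. The BDI-II analysis and its sample size are untouched.

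**What to change.** 1. When the patient is put forward for randomisation, record one item: outpatient psychotherapy place or first appointment already arranged, yes or no. An item at recruitment would miss places found during the stay. One at t1 would come after allocation, when patients are to have been told their group.
2. Analyse the access outcome in all randomised patients, stratified by or adjusted for this item. A Mantel-Haenszel risk difference is suitable: if all place-holders succeed, that stratum causes no difficulty, whereas a logistic model with the item as covariate could fail to converge.
3. Report the result in patients answering no as a supporting analysis. This subset is fixed before allocation, so the randomised comparison within it is preserved.

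Eligibility and the primary BDI-II analysis stay unchanged. The cost is one extra item at a step where the protocol describes no patient questionnaire, so the unit has to collect it as part of the randomisation request. If few patients hold a place, the benefit is correspondingly small.
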